## Trial design

This is an open-label, parallel group, randomized trial that will test the feasibility and effectiveness of a peer coach intervention in lowering the levels of anxiety and/or depression in patients with KOA before and after TKR. All participants will receive the standard of care for patients at the Hospital for Special Surgery (HSS) undergoing TKR, which consists of an educational book and a pre-surgery class. Patients with KOA enrolled in the study will be allocated to either the peer coach intervention (*Moving Well*) group or the attention control (*Staying Well*) group through a block randomization scheme. Participants will receive 50 dollars for every data collection timepoint.

This protocol is written in accordance with guidelines from the CONsolidated Standards of Reporting Trials (CONSORT) (see Fig. 1 for CONSORT) [47], and the Standard Protocol Items: Recommendations for Interventional Trials [48]. The institutional review board from HSS approved this study (protocol number 2019–1298).

**Fig. 1 Fig1:**
[figure not shown]
CONSORT diagram

### Study interventions

#### Overview of the *Moving Well* intervention

*Moving Well* consists of three main components (Fig. 2): an exercise program delivered through online videos, positive thinking (principle of CBT) training, and peer support with education on TKR, provided through weekly phone sessions between a peer coach and a participant for 12 sessions, 7 sessions in the 7 weeks pre-TKR, and 5 sessions for 5 weeks post-TKR. Table 2 details the curriculum of *Moving Well.* Each session of the intervention is scripted in the peer coach manual with all the content that the peer coach is responsible to deliver during each of the calls. The participant will have an Activity Book, which will contain the same content as the peer coach manual but with tables, and space to complete the daily activities that are assigned to them by the peer coach.

**Fig. 2 Fig2:**
[figure not shown]
*Moving Well* components

**Table 2 Tab2:** Moving Well peer coach arm schedule

Session	Objectives	PALS Questions & Answers
1. Introduction to the *Moving Well* Program	1. Introduce the *Moving Well* program 2. Introduce the Patient Activated Learning System (PALS) 3. Discuss the rules and responsibilities of the program 4. Discuss daily exercises	• None
2. Total Knee Replacement, the Relationship Between Mood and Pain, and Daily Exercise	1. Discuss the impact of pain and stress on living a healthy life and the goals of the *Moving Well* program 2. Discuss the **3 Steps** to achieve positive thinking that facilitate living a healthy life 3. Discuss the relationship between mood and pain 4. Discuss daily exercises	• What is osteoarthritis (OA)? • What is a total knee replacement (TKR)? • What is physical therapy? • What are the benefits of exercise? • What is the connection between pain and mood?
3. Negative Thoughts, Stress Reduction, and the Daily Exercise Program	1. Discuss negative thoughts and how to manage them 2. Practice stress reduction techniques 3. Discuss daily exercises	• What can I do about difficult emotions? • What is guided imagery and how can it help me? • How does mindfulness work? • How can I reduce stress? • Review the “Deep Breathing” exercise • Review the “Muscle Relaxation” exercise
4. “Awfulizing”, Physical Activity, Stress, and Pain	1. Introduce “Awfulizing” or “Spiral of Doom” 2. Discuss relationship between physical activity, stress, and pain 3. Discuss daily exercises	• How can I exercise when I’m in pain? • Does exercise help my pain from osteoarthritis (OA)?
5. Social Support and the Daily Exercise Program	1. Discuss social support and the importance of family and friends 2. Discuss daily exercises	• How can family and friends help me recover from total knee replacement (TKR)? • How can I have a better recovery after total knee replacement (TKR)?
6. Keeping Up with the *Moving Well* Steps	1. Discuss monitoring of mood, pain, and exercises 2. Prepare for knee replacement 3. Discuss the study visit 4. Discuss daily exercises	• What can I do about muscle tension?
7. The Safe Use of Opioids and Physical Therapy After Surgery	1. Discuss how to use opioids responsibly 2. Understand the importance of physical therapy after surgery 3. Discuss daily exercises	• How long should I expect to take opioids after my total knee replacement (TKR)? • How important is physical therapy after total knee replacement (TKR)? • How long does it take to recover from total knee replacement (TKR)?
**Surgery**		
8. Post-TKR Recovery and Planning for the Future	1. Discuss plans for knee replacement recovery 2. Discuss *Moving Well* plans for the rest of the program	• None
9. Post-TKR Recovery and Planning for the Future	1. Monitor progress with physical therapy 2. Discuss monitoring of pain, mood, and the 3 steps to achieve positive thinking	• None
10. Post-TKR Recovery and Planning for the Future	1. Monitor progress with physical therapy 2. Discuss monitoring of pain, mood, and the 3 steps to achieve positive thinking	• None
11. Post-TKR Recovery and Planning for the Future	1. Monitor progress with physical therapy 2. Discuss monitoring of pain, mood, and the 3 steps to achieve positive thinking	• None
12. Post-TKR Recovery, Questions, and Closure	1. Monitor progress with physical therapy 2. Discuss monitoring of pain, mood, and the 3 steps to achieve positive thinking 3. Close off the *Moving Well* program and discuss your next steps	• None

#### *Moving Well*: education materials-Patient Activated Learning System (PALS)

The TKR educational materials for the *Moving Well* group are available on the Patient Activated Learning System (PALS) website (www.palsforhealth.com) and are listed in Table 2. The PALS is a publicly available educational and empowerment resource informed by SCT designed to provide engaging, easily understood, and well-researched facts for people who want to know more about health, medicine, and diseases [49]. The content in the PALS is evidence-based and peer-reviewed. This content is translated into patient-facing text in plain language, aiming for a seventh-grade reading level. Some content is accompanied by visuals or short videos and a “sticky soundbite” to reinforce the single learning objective for each module, known in the PALS parlance as a renewable knowledge object (RKO). Each RKO includes an assessment question about the information that the reader has just reviewed.

#### *Moving Well*: exercise program

The pre-and post-surgery exercise program was designed by a certified physical therapist ([name]), who has extensive experience in TKR rehabilitation. The exercise program will be delivered to participants through online videos recorded by certified doctors in physical therapy from Weill Cornell Medicine (WCM). The videos use people with KOA to demonstrate the exercises. The program focuses on strengthening hip, core, and thigh muscles as well as increasing the knee range of motion. The exercise program allows the participant to select an individualized goal (advanced exercises vs. elementary exercises) based on their self-perceived ability.

#### *Moving Well*: principles of cognitive behavioral therapy and positive thinking

During each telephone session, the participants will learn and practice positive thinking, which consists of 3 main steps: *Identify* negative thinking; *Replace* negative thinking with positive thinking; *Practice* positive thoughts and/or healthy behaviors (e.g., exercise, mindfulness) [27, 28]. Each participant is required to monitor their daily mood and negative thoughts, then replace those thoughts with positive thoughts and/or practice positive action. This monitoring process will create self-awareness of their anxiety or depressive symptoms so that they can engage in healthier behaviors. Participants will be instructed on how to perform stress-reduction breathing exercises, meditation, and guided imagery to help manage anxiety and/or depressive symptoms. The CBT component of *Moving Well* will be a facilitator for each participant to decrease their fear of exercising while experiencing pain so that they can increase their self-efficacy in participating in the required, and often challenging, rehabilitation process after TKR.

#### *Moving Well*: peer coach

Peer coaches are not health professionals, they are individuals who have KOA and a history of TKR. Peer coaches will serve as role models and increase participants’ self-efficacy, which is one of the main tenets of the SCT. The role of the peer coach will be to provide support and coaching to each participant so that they successfully complete the activities and assignments of the intervention. The coaching and support by a person who already experienced the same event (had a TKR) will increase the likelihood of behavior change [30, 43, 50, 51]. They will also ensure that participants complete the daily monitoring activities. This will serve to guarantee that participants are completing the activities of the intervention as intended.

The inclusion criteria for peer coaches will be, having KOA and history of TKR at least 12 months before enrollment, and being 60 years of age or older. Once a person who has had TKR meets the criteria to be a peer coach, they will be interviewed by the research team to assess their communication skills. The research team will review each candidate and will document the reasons for not including a candidate as a peer coach. Peer coaches will be considered research subjects and will be consented before starting peer coach training.

#### Peer coach training

Peer coach training is modeled on a previously published approach [52]. Peer coaches will be scheduled for virtual training meetings. There will be a total of 15 web conference training sessions over 6 months, for up to 6 h a week. Peer coaches will be compensated on an hourly basis for the training and all subsequent interactions with the participants in the peer coach intervention group. Table 2 has details of the *Moving Well* curriculum, which is the curriculum that peer coaches will be trained on during the 6-month virtual training.

Before each training session, peer coaches-in-training will need to review the learning materials on PALS, listen to recordings of mock sessions between a peer coach and a participant, review the *Moving Well* participant Activity Book, and review the relevant session in the Peer Coach Manual. During training meetings, peer coaches will receive brief didactic education on the content of the *Moving Well*session assigned for the day, listen to mock sessions, practice delivering the session with a partner, and discuss their performance with the research team and other peer coaches [53]. Every week, peer coaches in training will be paired to practice delivering the session covered in the latest conference on their own time, in preparation for certification of that session. During the certification session, a coach-in-training will deliver the assigned session to a member of the research team over the phone, who will play the role of the participant. The research team will use a checklist to assess proficiency and communication skills during the call (Supplementary File 1). Peer coaches will be approved as peer coaches by members of the research team once they receive scores of 90% or more in all sessions, and each coach will have an opportunity to re-take the certification session if they do not achieve the required score. All peer coaches must pass all certification sessions to be able to work with a participant of *Moving Well.*

Peer coach training will also include two Motivational Interviewing (MoI) skills training meetings with the research team and only two coaches at a time. Each MoI training meeting will include the following activities: 1) Practicing MoI skills using role-playing scripts where coaches will alternate their roles between coach and participant under the supervision of the research team. 2) Reinforcing skills with live feedback and encouragement, allowing peer coaches to critique each other’s skills and propose ways for improvement on techniques like “rolling with resistance”, “action planning”, and the use of the MoI-style open-ended questions, affirmations, reflective listening, and summaries (OARS).

#### Peer coach retention

The strategies that we will use to retain coaches include ensuring timely payment for work and continuing education/training with opportunities for practicing skills. Ongoing support will be provided through weekly group conference calls outside of training time. These conference calls are used to problem-solve any challenges encountered, make sure they receive the support that they need to excel as peer coaches, and help build group identity within the peer coaches.

#### *Staying Well*: attention control arm

The subjects in the *Staying Well* attention control group will receive 12 weekly calls (7 before and 5 after TKR) from research assistants. These calls will be similar in length to those of *Moving Well* and cover topics not related to those of *Moving Well or TKR* (Table 3). These attention calls will help determine if providing a patient with attention and information not directly related to TKR and rehabilitation will yield the same outcomes as providing specific information and guidance for TKR.

**Table 3 Tab3:** Staying Well attention control arm schedule

Session	Objectives	Health Topics
**Session 1**	A. Overview of the goals and objectives of the program B. Get to know each other	Introduction to the Program
**Session 2**	A. To learn how to read nutritional facts labels B. To discuss the importance of fruits and vegetables	Healthy Eating and You: Part 1 a. Reading Nutritional Facts Label^a^ b. Portion Sizes^a^ c. Fruits and Vegetables^a^ d. Making Healthy Food Choices^a^ e. What is a healthy diet?
**Session 3**	A. Learn about heart-healthy fats and proteins B. Learn about grains and dairy C. Learn about fiber rich food	Healthy Eating and You: Part 2 a. Healthy Fats vs. Less Healthy Fats^a^ b. Powered by Protein^a^ c. Meat, Heart disease, and Cancer^a^ d. Plant-Based Protein^a^ e. Grains and Dairy^a^ Fiber-rich Foods
**Session 4**	A. To learn discuss how to put into practice what you have learned about healthy eating B. To learn about healthy eating outside of the home C. To discuss recipe modifications for heart healthy recipes	Healthy Eating and You: Part 3 a. Practice Healthy Eating b. Healthy Eating Outside of the Home^a^ c. Social Events and Your Health^a^ d. Healthy Recipe Modifications^a^
**Session 5**	A. To learn about added sugars B. To learn about sugar-sweetened beverages To learn about menu planning	Healthy Eating and You: Part 4 a. Drinking Water^a^ b. Sugar-sweetened Beverages^a^ c. Sports drinks and energy drinks^a^ d. Added Sugar^a^ e. Snacks and Treats^a^ Menu Planning^a^
**Session 6**	A. To learn the symptoms of high blood pressure B. To provide an overview of the treatment for high blood pressure	High Blood Pressure a. What is high blood pressure? b. Symptoms of high blood pressure c. Treatments for high blood pressure d. Salt and high blood pressure Blood pressure and my body
**Session 7**	A. To learn about good and bad cholesterol B. To learn how and when to treat high cholesterol	Cholesterol a. What is cholesterol? b. Good vs. Bad Cholesterol c. Health Complications with High Cholesterol d. Treatments for High Cholesterol e. Atherosclerotic Cardiovascular Disease (ASCVD) risk, Heart Failure, and Stroke f. Getting a cholesterol test
**Session 9**	A. To learn about the different doctors that care for you (primary care doctor and specialist) B. To learn about disease prevention	Your Doctors and You a. What is a primary care provider? b. What is a specialist or specialty doctor? The importance of yearly checkups
**Session 10**	A. To learn about cancer prevention and early detection	Cancer Screenings a. Colorectal Cancer b. Cervical Cancer c. Prostate Cancer Breast Cancer
**Session 11**	A. To learn about the harmful effects of tobacco use B. To learn about secondhand smoking and it’s affects C. To learn about the cancers caused by smoking	Tobacco Use a. Tobacco Use Screening b. Tobacco Alternatives c. Secondhand smoking d. Lung cancer screening Smoking related cancers
**Session 12**	A. To review the health risk of alcohol consumption	Alcohol and My Health a. Alcohol consumption recommendations b. Alcohol Misuse c. Health Risks of Drinking Alcohol Interactions Between Medicines and Alcohol

^a^Content adapted from [name], RDN, CSCS on behalf of the StrongPeople Program (formerly known as the StrongWomen Program)

#### Guidelines for surgery cancellation, postponement, and concomitant care

Participants in both arms of the study will be free to withdraw at any time. In the event of total knee replacement surgery postponement, the participant will be allowed a maximum 2-week interruption in the study schedule. If there is a more than 2-week delay in surgery and therefore a greater than 2-week gap in the study schedule, or the surgery is cancelled, the reason/s for postponement or cancellation will be collected, and the participant will undergo an exit interview, and no further data will be collected. Participants who have taken part in an exit interview will be allowed to rejoin the study later if they wish to, and continue in their previous intervention allocation, however, they must start from the beginning of the intervention schedule. Participants in either arm of the study are permitted to receive any concomitant care related to their knee OA or TKR while in the study.

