### Study population and sample size

The participants of the study will be people with KOA who are 50 years of age or older, have a TKR scheduled in 8 weeks or more, speak English, have access to a computer, the internet, and a working phone. We will exclude people who are unable to exercise (wheelchair-bound or bedbound), have a history of any joint replacement surgery, or have any rheumatic disease other than KOA.

The peer coaches of *Moving Well* will be people with KOA who had a TKR at least 12 months before they initiate their training as peer coaches of the intervention. This study will have 5 peer coaches.

The sample size estimation assumed four repeated measures, a range of intra-class correlations (0.05 to 0.20) for the repeated measures, and a Bonferroni-adjusted overall type I error of 5% (after controlling for two primary outcomes). We estimate a 20% attrition rate and will recruit 93 subjects, resulting in 37 participants in each arm of the study (total of *N* = 74 completers). The trial is designed to have at least 80% power to detect a standardized effect size of d = 0.5 or 0.5 standard deviations between the intervention and attention control arms. The standardized effect size is equivalent to a 2.7-point change in the PHQ-8 score, and a 1.6-point change in the GAD-7 score.

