### Participant recruitment, enrollment, and randomization

Participants will be recruited from the orthopedic clinics at HSS in Manhattan, New York. The target sample will be 74 patients. To enroll 74 participants, we expect to screen 500 individuals with KOA who are scheduled to undergo TKR. We will monitor recruitment success including screen failure rates, to inform the design of the planned larger study to follow this one. Patients who meet the inclusion criteria will be contacted by research staff and invited to join the study. Once a patient meets the criteria and we have obtained informed consent, they will be scheduled for their first data collection visit, either in person or virtually, with a blinded research assistant, and subsequently randomized. Block randomization will be used in REDCap to randomize participants to either the *Moving Well* arm or the *Staying Well* arm.

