### Data analysis

We will use descriptive statistics, t-tests, and Chi-square tests as appropriate to compare patients in each study arm. We will assess group differences between baseline and the week before TKR, 6 weeks after TKR, and 6-, 12-, and 24-months after TKR with parametric and nonparametric analyses including one-sample t-tests, Wilcoxon rank sum, and Chi-square tests or Fisher’s exact test of proportions, as appropriate. All tests will be two-sided (unless otherwise stated) and the overall type I error will be maintained at 5%.

We will use linear and generalized linear mixed effects regression models to analyze the repeated measures of all outcomes. Although a significant treatment*time interaction will conclude rejection of the hypothesis, in this pilot study we will focus on obtaining estimates of baseline adjusted treatment effects at the end of treatment as preliminary evidence of effectiveness to power a future trial. We will correct the inflation of the type I error due to multiple primary outcomes using Holm’s stepdown procedure. Due to the exploratory nature of the secondary outcomes, we will not adjust the type I error. Our mixed models provide valid inferences when data are missing at random. However, we will also test the plausibility of this assumption and repeat our analysis using pattern-mixture models [65].

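### Outcome collection stops when surgery is cancelled or delayed by more than 2 weeks, an event that follows randomisation and that the arms could influence differently

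*Protocol article*

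**What the plan says.** The rule is in the protocol article, under Guidelines for surgery cancellation, postponement, and concomitant care. A postponement may interrupt the study schedule by at most 2 weeks. After a longer delay or a cancellation, staff record why it happened; then "the participant will undergo an exit interview, and no further data will be collected". Exited participants "will be allowed to rejoin the study later if they wish to, and continue in their previous intervention allocation". Anyone who does so repeats the calls from session 1.

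Four other parts of the article bear on this:

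- **Timing of randomisation.** Eligible patients "have a TKR scheduled in 8 weeks or more" (Study population and sample size). After consent, "they will be scheduled for their first data collection visit, either in person or virtually, with a blinded research assistant, and subsequently randomized" (Participant recruitment, enrollment, and randomization). Seven weekly calls then precede surgery in both arms.
- **Primary outcome.** PHQ-8 and GAD-7 are compared between arms at 6, 12 and 24 months after surgery (Primary and secondary outcomes). A blinded team member telephones participants who have not completed their surveys, in order to limit missing data.
- **Missing data.** "Our mixed models provide valid inferences when data are missing at random" (Data analysis). The sentence that follows commits to examining that assumption and repeating the analysis with pattern-mixture models.
- **Follow-up schedule.** Table 4 lists five PHQ-8 and GAD-7 assessments after baseline: 1 week before surgery, then 6 weeks, 6 months, 1 year and 2 years after it.

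**The concern.** Whether surgery goes ahead on time is settled after randomisation. In the weeks before surgery only Moving Well provides exercise, positive-thinking training and education about knee replacement, and its targets include catastrophizing, fear of pain and unrealistic expectations of the operation (Table 1). Staying Well avoids these topics by design. Differences of this kind could plausibly change symptoms, expectations or willingness to proceed, and so the share of each arm whose surgery is postponed or cancelled. Mood and pain may also affect that decision, and mood is the primary outcome.

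Stopping data collection on such an event creates missing primary outcomes that may depend on both arm and prognosis. The pilot's treatment estimate is meant to inform the power of a later trial, so any bias would carry forward. The loss is also partly avoidable: a patient whose operation is late but takes place has well-defined 6-, 12- and 24-month post-surgery timepoints, and the surveys can be done remotely or by telephone.

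**Working it through.** **1. The plan's own sample size.** Inputs (Study population and sample size; Data analysis): 20% attrition, 37 completers per arm, d = 0.5, two primary outcomes sharing a 5% error rate (0.025 each, two-sided), four repeated measures, intra-class correlation (ICC) 0.05 to 0.20.

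- Recruitment: 74 / (1 − 0.20) = 92.5, rounded up to 93. This reproduces the stated figure.
- Power: the SD of a mean of m equally correlated measures is √[(1 + (m − 1) × ICC) / m]. At ICC 0.20 with 37 per arm, m = 4 gives SD 0.632 and power 87.7%. With m = 3 (three post-baseline measures, baseline as the fourth) the SD is 0.683 and power 81.8%. The claim of at least 80% holds.

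**2. What an exited participant contributes.** In Table 4 the first assessment after baseline is 1 week before surgery. Someone who exits before surgery and does not rejoin therefore contributes baseline and at most that one further survey. None of the three primary timepoints is observed.

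**3. Possible bias.** Let e be the exit share in an arm and D the mean outcome of leavers minus that of stayers, in SD units, taken as equal in both arms. The stayers' mean is then the full-arm mean minus e × D, so

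bias in the completer difference = −(e_MW − e_SW) × D.

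The documents give neither e nor D. The values below are assumptions.

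| Difference in exit share | D = 0.5 SD | D = 1.0 SD |
|---|---|---|
| 0 points | 0 | 0 |
| 10 points (e.g. 20% v 10%) | 0.05 SD | 0.10 SD |
| 15 points (e.g. 25% v 10%) | 0.075 SD | 0.15 SD |

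The non-zero entries are 10% to 30% of the 0.5 SD design effect (0.05/0.5 and 0.15/0.5). The article equates 0.5 SD with 2.7 PHQ-8 points and 1.6 GAD-7 points, so 1 SD is 5.4 and 3.2 points. The range is then 0.27 to 0.81 PHQ-8 points and 0.16 to 0.48 GAD-7 points. The sign depends on which arm loses more participants and on whether leavers score higher or lower.

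**4. Power, if surgery exits came on top of the 20% attrition (also assumed).** Completers = 93 × 0.80 × (1 − extra exit rate). Power is at ICC 0.20.

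| Extra exits | Completers | Power, m = 4 | Power, m = 3 |
|---|---|---|---|
| 5% | 70.7 | 86.0% | 79.8% |
| 10% | 67.0 | 84.0% | 77.4% |
| 15% | 63.2 | 81.6% | 74.8% |
| 20% | 59.5 | 79.1% | 72.0% |

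If the 20% already includes surgery exits, this loss does not arise. Power is the lesser issue, because more recruits would restore it but would not remove a bias.

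**The case against.** A reader might infer that the rule is a post-randomisation exclusion that turns the trial into a comparison of patients operated on schedule. The text does not go that far. It ends data collection but does not remove anyone from the analysis set. Delays of up to 2 weeks stay in, and those who rejoin keep their allocated arm. A mixed model can use whatever was recorded before exit, and the pattern-mixture analysis is a stated response to data not missing at random. All of this stands, and it lowers the severity. It does not remove the point, because pattern-mixture results rest on assumptions about outcomes nobody observed, and here many of those outcomes could have been observed.

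The size is also uncertain. Delays for scheduling reasons may be unrelated to arm. The completer formula is cruder than the planned baseline-adjusted model. Even 0.15 SD is below the standard error of a single-timepoint difference at 37 per arm, √(2/37) = 0.23 SD. That stands too, although a systematic error is not excused by being smaller than the random one.

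Outcomes are defined relative to surgery, so a cancelled case has no post-surgery timepoint, and including it changes the question asked. This is right for cancelled cases but does not apply to delayed ones.

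Three further inferences are not supported:

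- **Baseline of rejoiners.** The article does not say which baseline counts. A condensed article may leave that to the full protocol, so it is not a fault here.
- **Completion rate.** Extra surveys would not raise intervention completion, since sessions 8 to 12 follow surgery.
- **Surgery delay ignored.** Reasons for postponement are recorded and drop-outs are invited to interview, so reporting by arm is a refinement.

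**Conclusion.** The point holds in limited form. A stated rule stops primary-outcome collection on a post-randomisation event that the allocated arm could influence, and no later analysis can recover what was not collected. The documents do not show that exits will differ by arm, and they do not exclude exited participants from analysis. The bias therefore cannot be sized from the documents. It is zero under the completer formula if exit rates are equal, and about 0.05 to 0.15 SD under the assumed 10 to 15 point differences and 0.5 to 1.0 SD gaps. The case is clearest for patients whose surgery is late but goes ahead. Given the partial mitigation already planned, this is something the trial should fix; it does not invalidate the design.

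**What to change.** Separate stopping the call schedule from stopping follow-up. The rule on calls, including restart on rejoining, remains the investigators' decision. For data:

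1. Keep collecting the self-report surveys, remotely or by telephone, from every randomised participant who has not withdrawn consent.
2. When surgery is delayed, date the post-surgery surveys from the actual operation.
3. When surgery is cancelled, collect at times counted from the originally scheduled date, and report results with and without these participants, because they have no post-surgery timepoint.
4. Analyse everyone as allocated, counted once, with the on-schedule subset as a sensitivity analysis.
5. Report delay and cancellation by arm.

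**Cost.** Expected attrition is 93 − 74 = 19 people. If all of it were surgery exits, payments would be at most 19 × 5 follow-ups × 50 dollars = 4,750 dollars, plus modest staff time. The other downside is some dilution of the effect from participants without timely surgery, which the sensitivity analysis would show.
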